**Control group:**

Non-intervention but usual care

Participants in this group will be informed via email that they are in the no treatment group but will be emailed an online link to complete the post-intervention questionnaire in two weeks’ time.

Participates in the non intervention group will receive a complementary LLLA after the two weeks trial.

**How the planned methods achieve the aim or research questions**

**Primary outcomes:**

The primary outcome for this study is feasibility of the two weeks LLLA therapy for office workers with SNP. Feasibility will be assessed by measuring: 1) recruitment and completion rates (No. of referred, No. of eligible, No. of enrolled, No. of withdrawals, trial recruitment rate, and trial completion rate), 2) patient safety (No. and severity of adverse events), and 3) treatment adherence (No. of completed sessions and missed sessions). Participants’ motivation and challenges to participation, withdrawal, missed sessions and non-compliance to intervention will be investigated, as will their attitude, and experience in participating the trial.

**Secondary outcomes:**

The questionnaires used in this project to assess the outcomes including demographics data, VAS, SF-MPQ, WPAI:SHP, SF-12, and the participants’ motivation, challenges, and attitude of participating the trial. As a feasibility study, questions on non-pharmacologic therapy and out-of-pocket (OOP) expenses will also be included.

**Statistical analysis:**

For the primary outcome, rates of recruitment (numbers consented/eligible), completion (undertaken baseline and follow-up tests), adherence (participant completed sessions/number of sessions), and adverse events (number and number per participant hour) will be calculated. Secondary outcome will be assessed following intention-to-treat principles. Repeated measures ANOVA will be conducted to assess changes in secondary outcomes throughout the study. This model allows inclusion of missing data in an intention-to-treat analysis without imputations (e.g. last-observation-carried-forward). If necessary, analysis will be adjusted for baseline levels and potential confounding factors. Normality assumptions will be assessed using the Shapiro-Wilk test. Statistical significance will be set at an alpha level of 0.05. Corrections will be applied to all analysed outcomes to account for multiple comparisons.

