**Intervention group:**

In addition to usual care, participants will receive LLLA from a licensed acupuncturist at ECU Acupuncture Research Clinic. 10-20 minutes per session, three times a week for two weeks. The parameters of 3B Laser Pen (200mW) used for the intervention are wavelength of 808 nm in continuous wave mode, each pressure point receives 20 seconds of energy (4J) with 5 minutes being the maximum treatment time (60 J). At the end of two weeks receiving the therapy, participants will receive an online link to complete the post-intervention questionnaires.

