**Recruitment**

**Study population**

Although it is feasible to consist of 30 participants per group (Hertzog, 2008), some dropout is likely during the entire trial process. We estimate an attrition of 15% based on the attrition of 12% reported by previous study. Taking these two factors into account the sample size for this study is determined to be 70, with 35 participants in each of the two study groups.

Seventy Office worker aged 18-65, working more than 28 h a week with sedentary office work and have moderate to severe SNP (VAS > 5/10 & SF-MPQ >2/45) for more than three months will be recruited for this trial.

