**Statistical analysis**

For the primary outcome, rates of recruitment (numbers consented/eligible), completion (undertaken baseline and follow-up tests), adherence (participant completed sessions/number of sessions), and adverse events (number and number per participant hour) will be calculated. Secondary outcome will be assessed following intention-to-treat principles. Repeated measures ANOVA will be conducted to assess changes in secondary outcomes throughout the study. This model allows inclusion of missing data in an intention-to-treat analysis without imputations (e.g. last-observation-carried-forward). If necessary, analysis will be adjusted for baseline levels and potential confounding factors. Normality assumptions will be assessed using the Shapiro-Wilk test. Statistical significance will be set at an alpha level of 0.05. Corrections will be applied to all analysed outcomes to account for multiple comparisons.

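### The protocol says repeated measures ANOVA keeps participants with missing data in an intention-to-treat analysis; with two time points it is an unadjusted change-score comparison in completers

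*Protocol*

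**What the plan says.** The protocol has two Statistical analysis sections, one after Secondary outcomes and one before Risk, with the same text. On the secondary outcomes they set out three things:

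- The principle to be followed is intention to treat, and the method named for it is repeated measures ANOVA, used to examine change over the study.
- That method is then credited with a way of handling incomplete follow-up: "This model allows inclusion of missing data in an intention-to-treat analysis without imputations (e.g. last-observation-carried-forward").
- Adjustment for baseline and confounders is permitted, but only where it is judged necessary, and no rule is given for deciding.

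No mixed model or other likelihood-based method is named.

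There are two measurement occasions. The baseline survey is completed before randomisation. The Intervention group section then says: "At the end of two weeks receiving the therapy, participants will receive an online link to complete the post-intervention questionnaires". The Control group section sends its link after the same two weeks. Completion is defined in line with this: "completion (undertaken baseline and follow-up tests").

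On dropout, Study population says: "We estimate an attrition of 15% based on the attrition of 12% reported by previous study". It arrives at 35 participants per group, 70 in total.

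**The concern.** The named model and the property claimed for it do not match. Classical repeated measures ANOVA needs both measurements from each person. Even if software keeps the baseline row, someone with one measurement contributes nothing to the within-person contrast. An analyst following the text must give up either the named model or the claimed property. If the model is kept, a completer analysis will be reported as intention-to-treat.

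The resulting comparison is also an unadjusted change score. Change normally depends on the starting value, and the entry threshold of VAS above 5 adds regression to the mean. If the participants who remain differ at baseline between arms, that difference carries into the estimated effect. Efficacy is a stated secondary objective, and this is the only efficacy analysis the protocol specifies.

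**Working it through.** **1. The protocol's own figure.** Study population starts from 30 per group ("Although it is feasible to consist of 30 participants per group").
- 30 × 1.15 = 34.5, rounded up to 35.
- 30 / (1 − 0.15) = 35.3, rounded up to 36.
- At 12%: 30 / (1 − 0.12) = 34.1, rounded up to 35.

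The stated 35 per group reproduces to within one participant and is not in dispute.

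**2. How many are analysed.**
- At 15%: 70 × 0.85 = 59.5 analysed (35 × 0.85 = 29.75 per arm); 70 × 0.15 = 10.5 dropped.
- At 12%: 70 × 0.88 = 61.6 analysed; 70 × 0.12 = 8.4 dropped.

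**3. What the test is.** With two time points, let d = week 2 − baseline. The group-by-time F equals the squared two-sample t statistic on d among people who have d. In a simulated data set of 70 with 5 dropouts per arm, both routes gave 0.3171, with 58 error degrees of freedom from 60 completers. On the same data a linear mixed model used 130 observations from 70 people (70 + 60); ANOVA used 120 from 60 (60 × 2). This step needs no assumption about why people drop out.

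**4. Precision.** Assume equal variance σ² at both times and correlation ρ. The per-person variance is 2σ²(1 − ρ) for change and σ²(1 − ρ²) for a baseline-adjusted comparison. The ratio of adjusted to change is (1 + ρ)/2, which is 0.65, 0.75 and 0.85 at ρ = 0.3, 0.5 and 0.7.

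**5. Possible bias.** Under no treatment effect, with equal SDs, linear regression to a common mean μ, and dropout depending only on baseline b, the expected change given b is −(1 − ρ)(b − μ). The bias in the completer change comparison is therefore −(1 − ρ)Δ, where Δ is the completers' mean baseline on LLLA minus that in control.

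Simulation inputs, all assumed: 35 per arm, latent VAS mean 5.5 and SD 2, selected above 5, about 5% dropout on LLLA, and 28–29% in control rising with baseline. One set of 4000 runs gave:

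| ρ | Bias, VAS points | Implied Δ = −bias/(1 − ρ) | Size of bias over runs with other dropout curves |
|---|---|---|---|
| 0.3 | −0.243 | 0.347 | 0.21–0.26 |
| 0.5 | −0.186 | 0.372 | 0.16–0.18 |
| 0.7 | −0.103 | 0.343 | 0.10–0.11 |

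The implied Δ is nearly constant, as the formula requires. The estimate's sampling SD was about 0.39 to 0.55. Even the largest bias over the smallest SD is 0.26/0.39 = 0.67 of a standard error.

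**6. Where the bias comes from.** Variants of the same simulation separate the causes:
- A complete-case model with baseline as covariate, deleting exactly the same people, had bias of at most 0.014. Simulation error at 4000 runs and SD 0.5 is 0.5/√4000 = 0.008.
- Dropout of 5% against 25%, unrelated to baseline: change-score bias below 0.01.
- About 14% in both arms, rising with baseline equally: below 0.01.
- About 10% against 19%, milder slope: 0.06 to 0.12.

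**The case against.** Several points on the other side stand in whole or in part.

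- **Loose naming.** The sentence describes a likelihood-based repeated measures model accurately, so the intended analysis may be sound and only its name wrong. Nothing in the protocol settles this; naming the model would.
- **Baseline adjustment is already mentioned.** Where it is applied, the bias in step 5 disappears. But it is optional, and it does not make the missing-data sentence true.
- **The loss is budgeted.** About 30 completers per arm is what the sample size aims for, so deletion does not leave the trial short of its target. Participants with only a baseline value would add little precision to a mixed model.
- **Secondary outcomes in a feasibility pilot.** Recruitment, completion, adherence and adverse-event rates are untouched.
- **It could be left to a statistical analysis plan.** That holds for detail such as a sensitivity analysis. It does not hold for a property that the protocol itself states, and states wrongly.

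A reader might infer more: that deleting participants itself produces a spurious LLLA benefit, or that unequal dropout between arms is enough to do so. Step 6 supports neither. Bias needs dropout that depends on baseline differently by arm, together with an analysis that ignores baseline. The protocol gives no evidence of such a mechanism. Controls are told that they are untreated, and Psychological Risks anticipates disappointment, but they are also offered LLLA after the two weeks, which could help retention.

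**Conclusion.** The statement is wrong as written, in both places. The named method would analyse about 59 or 60 of 70 participants at the protocol's own attrition, by an unadjusted change-score comparison that cannot be described as keeping participants with missing data. That conclusion rests only on the two-time-point design and the 15% figure.

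The loss of precision is general: the adjusted variance is 65% to 85% of the change-score variance for correlations of 0.3 to 0.7, assuming equal variances. The bias is only a possibility. At roughly 0.1 to 0.25 VAS points it is below one standard error, it depends wholly on an assumed arm-specific dropout mechanism, and it comes from not conditioning on baseline. It is absent if dropout is unrelated to baseline or related to it equally in both arms. The point should be fixed, but it concerns secondary outcomes only and does not threaten the feasibility objective.

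**What to change.** In both Statistical analysis sections, replace repeated measures ANOVA with one of the following:

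1. A likelihood-based linear mixed model with baseline and week 2 as responses, a common baseline mean across the randomised arms, and the arm difference at week 2 as the estimate. All randomised participants then contribute under a missing-at-random assumption, which should be stated.
2. A model for the week-2 value that always includes baseline as a covariate, described plainly as a complete-case analysis.

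In either case, remove the sentence that attributes the missing-data property to ANOVA and make the baseline adjustment unconditional. A delta-shift sensitivity analysis for participants without follow-up is optional and can be left to the statistical analysis plan. The cost is a wording change in two identical paragraphs; no extra data or participants are needed.

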**Recruitment**

**Study population**

Although it is feasible to consist of 30 participants per group (Hertzog, 2008), some dropout is likely during the entire trial process. We estimate an attrition of 15% based on the attrition of 12% reported by previous study. Taking these two factors into account the sample size for this study is determined to be 70, with 35 participants in each of the two study groups.

Seventy Office worker aged 18-65, working more than 28 h a week with sedentary office work and have moderate to severe SNP (VAS > 5/10 & SF-MPQ >2/45) for more than three months will be recruited for this trial.

**Inclusion criteria**

1) aged between 18-65 years

2) working more than 28 h a week with sedentary office work

3) moderate to severe SNP (VAS > 5/10 & SF-MPQ > 2/45) for more than three months

**Exclusion Criteria**

1) with a serious health conditions of the neck and shoulder

2) pregnant

3) with cancer

4) high sensitivity to light

**How will participants be identified and initially contacted including screening processes?**

The snowballing process and public advertisement can identify potential participants. People interested in participating in the study will be encouraged to contact the research team via email for an eligibility check. We will send online screening checklist, including the SF-MPQ and VAS, to assess their suitability for participation.

**Data collection method and location including who will be responsible for the data collection**

Participation in this research project is voluntary. If one does not wish to take part, they do not have to. If participant decided to take part and later changed their mind, they are free to withdraw from the project at any time. If they decide to withdraw from the project after the data has been analysed, we will not be able to remove the individual data as this cannot be identified.

If participant do decide to take part, they will be given the participant information letter and consent form to sign, and they will be given a copy of the information letter to keep. They decision to take part, or to take part and later withdraw, will not affect they relationship with the research team and any staff within the School of Nursing and Midwifery at ECU.

By signing the consent form, they consent to the research team collecting and using personal information about the participant for the research project. Any information obtained in connection with this research project that can identify participant will remain confidential. When all survey responses are returned to the research team, all data are automatically de-identified, and they will not be identifiable by any of their responses to the survey. They information will only be used for the purpose of this research project and it will only be disclosed with they permission, except as required by law.

It is anticipated that the results of this research project will be published and/or presented in a variety of professional forums. In any publication and/or presentation, the information will be provided in such a way that participants cannot be identified, except where requested for specific reasons, and then they will be asked to provide written consent.

In accordance with relevant Australian and/or Western Australian privacy and other relevant laws, participants have the right to request access to the information about them that is collected and stored by the research team. They also have the right to request that any information that they disagree to be corrected. They are encouraged to inform the research team member named at the end of this letter if they would like to access they information.

All data collected will be kept in accordance with ECU’s Data Management Policy. Electronic data will be stored on a secure Microsoft SharePoint site provisioned by ECU’s IT Services and physical records will be stored as required in ECU’s Records Management Policy. The data will be retained for a period of seven years and destroyed, if appropriate at the end of the retention period. Data will be de-identified when stored and at the end of the retention period, the data will be destroyed, if appropriate under the State Records Act.

There are no foreseeable risks associated with participation in this research project.

We will advise participants of the outcomes via email communication. We also intend to publish our results in research journals and present them at research conferences locally, nationally and internationally. Participants' name or any other identifying information will not be included in any of the publications or presentations.

This research project will not start until we sought the approval of Edith Cowan University’s Human Research Ethics Committee under the National Health and Medical Research Council’s National Statement on Ethical Conduct in Human Research 2007 (Updated 2018).

**Statistical analysis**

For the primary outcome, rates of recruitment (numbers consented/eligible), completion (undertaken baseline and follow-up tests), adherence (participant completed sessions/number of sessions), and adverse events (number and number per participant hour) will be calculated. Secondary outcome will be assessed following intention-to-treat principles. Repeated measures ANOVA will be conducted to assess changes in secondary outcomes throughout the study. This model allows inclusion of missing data in an intention-to-treat analysis without imputations (e.g. last-observation-carried-forward). If necessary, analysis will be adjusted for baseline levels and potential confounding factors. Normality assumptions will be assessed using the Shapiro-Wilk test. Statistical significance will be set at an alpha level of 0.05. Corrections will be applied to all analysed outcomes to account for multiple comparisons.

**Risk**

**Physical Risks**

LLLA is cleared and approved by the Food and Drug Administration (FDA). It is safe and there are no foreseeable risks associated with participation in this research project. However, both the practitioner and the participants will wear an appropriate laser safety eyewear that match the laser wavelength and have sufficient optical density at that wavelength to protect the eye.

**Psychological Risks**

Participants in the Non treatment group may feel disappointed. They will receive a complementary LLLA treatment after the two weeks trial as our appreciation and acknowledgement of their time.

**Social Risks**

No foreseeable social risks associated with participation in this research project.
